# The effect of remote ischemic preconditioning on serum creatinine in patients undergoing partial nephrectomy: a study protocol for a randomized controlled trial

**DOI:** 10.1186/s13063-018-2820-3

**Published:** 2018-09-04

**Keywords:** Remote ischemic preconditioning, Partial nephrectomy, Acute kidney injury, Urinary biomarker

## Abstract

**Background:**

Acute kidney injury (AKI) may develop during partial nephrectomy due to ischemic reperfusion injury induced by renal artery clamping or surgical insult. The effect of remote ischemic preconditioning (RIPC) on reducing the renal injury after partial nephrectomy has not been evaluated in terms of urinary biomarkers.

**Methods/design:**

We will conduct a randomized controlled trial enrolling the patients who will undergo partial nephrectomy. In the study group, RIPC which consisted of four 5-min cycles of limb ischemia and reperfusion will be conducted after induction of anesthesia. Postoperative serum creatinine values, the incidence of AKI, and urinary biomarkers, including urinary creatinine, microalbumin, β-2 microglobulin, and *N*-acetyl-beta-D-glucosaminidase, will be compared between groups during the postoperative 2 weeks. Regional oxygen saturation on the skin of the contralateral kidney will be measured to evaluate the association between intraoperative regional oxygen saturation values and renal injury of the operating side.

**Discussion:**

We expect that our trial may demonstrate the effect of RIPC on mitigating the immediate postoperative renal injury and improving patient outcomes after partial nephrectomy. Moreover, our patients will undergo ^99m^Tc-DTPA radionuclide scintigraphy to calculate glomerular filtration rate 6 and 12 months after surgery. This data should show the long-term effect of RIPC.

**Trial registration:**

ClinicalTrials.gov, ID: NCT03273751. Registered on 6 September 2017.

**Electronic supplementary material:**

The online version of this article (10.1186/s13063-018-2820-3) contains supplementary material, which is available to authorized users.

## Background

Remote ischemic preconditioning (RIPC) refers to applying one or more cycles of brief, non-lethal ischemia and reperfusion to a distant organ or tissue, which is known to protect heart and other organs against acute ischemic insult [1–4]. To demonstrate the renal protective effect of RIPC, many clinical trials were published under various surgical settings. According to two recently reported meta- analyses, RIPC is beneficial to prevent the development of acute kidney injury (AKI) in cardiac or vascular procedures [5, 6]. A multicenter randomized trial reported that RIPC could reduce the incidence of postoperative AKI and renal replacement therapy during cardiac surgery [7]. However, according to the Cochrane Review, RIPC did not lead to significant differences in serum creatinine, need for dialysis and incidence of AKI in patients who underwent interventions that may result in ischemic renal injury [8]. Thus, there is still controversy about the protective effect of RIPC on the renal ischemic injury.

Partial nephrectomy has now become a standard treatment for localized renal small cell cancer [9, 10]. Partial nephrectomy can preserve normal renal parenchyma and kidney function. The incidence of postoperative AKI and chronic kidney disease were significantly lower after partial nephrectomy compared to radical nephrectomy [11–13]. However, during partial nephrectomy, the renal vascular pedicle usually needs to be temporarily clamped, leading to ischemia-reperfusion injury (IRI). AKI after partial nephrectomy still occurs frequently due to IRI and the incidence of AKI after partial nephrectomy has been reported to be as high as 39% [14].

Theoretically, we assumed that RIPC, which can prevent IRI, may reduce renal ischemic injury in patients undergoing partial nephrectomy. There are only two randomized controlled trials (RCT) which evaluated the effect of RIPC during partial nephrectomy [15, 16]. Although these studies suggested the renal protective effect of RIPC, one study did not measure biomarkers to detect renal injury [15] and another study measured serum biomarkers of neutrophil gelatinase-associated lipocalin (NGAL) and cystatin C only during the immediate postoperative period [16]. However, as other urinary biomarkers, including urinary creatinine, microalbumin, β-2 microglobulin, and *N*-acetyl-beta-D-glucosaminidase (NAG) are also available [17–22], the effect of RIPC can be evaluated with these biomarkers. Glomerular filtration rate (GFR) and split function of each kidney can be measured by technetium diethylene triamine pentacetic acid (^99m^Tc-DTPA) radionuclide scintigraphy. Since AKI can predispose to chronic kidney disease [23], the long-term effect of RIPC in terms of GFR measured by scintigraphy need to be evaluated.

Therefore, we hypothesized that RIPC may mitigate the IRI due to renal arterial clamping during partial nephrectomy, thereby, reducing the elevation in serum creatinine and urinary biomarkers of renal injury. We aimed to evaluate the effect of RIPC on postoperative renal function measured by serum creatinine, urinary biomarkers, and GFR measured by scintigraphy.

## Methods/design

The trial protocol was developed in accordance with the Standard Protocol Items: Recommendations for Interventional Trials (SPIRIT) guidelines [24] (Additional file 1). The SPIRIT Figure on the trial proceedings is added as Fig. 1. This trial is an ongoing, prospective, single-center, surgeon- and patient-blinded, randomized controlled trial.

**Fig. 1 Fig1:**
[figure not shown]
Standard Protocol Items: Recommendations for Interventional Trials (SPIRIT) Figure for the present study

### Setting and participants

Eligible participants are adults (≥ 20 years of age) who are scheduled to undergo open or laparoscopic or robot-assisted partial nephrectomy. We included patients with a normal contralateral renal function that will be confirmed as a preoperative split renal function of > 40% by the ^99m^Tc-DTPA radionuclide scintigraphy to compare the function of the kidney on the surgery.

Exclusion criteria are the patients with any of the following disease: clinically significant peripheral vascular disease affecting the upper arms, severe cardiopulmonary diseases (valvular or ischemic heart disease, heart failure, left ventricular ejection fraction < 40%, chronic obstructive pulmonary disease, forced expiratory volume in 1 s of < 40% of the predicted value), baseline chronic kidney disease (estimated GFR of < 30 ml per min per 1.73 m^2^ of body-surface area or preoperative serum creatinine level > 1.4 mg/dl), and hepatic failure (bilirubin level of > 1.2 mg/dl or international normalized ratio of > 2.0).

### Informed consent and ethical approval

The subjects to participate in the trial should be informed of all relevant information to this study in terms that they can easily understand. The subjects will be given enough time to consider and have the opportunity to ask questions about the study before deciding to participate in the study. In addition, the subjects should be informed that they will be randomly assigned to the experimental and control groups at a 1:1 ratio, and that they will receive no disadvantage by refusing to participate in the study. After a full explanation, written consent will be obtained from all participants by one of our co-authors. It is a right of the subject to refuse to participate, or to withdraw at any time, during the research period.

This study is being conducted in accordance with the Declaration of Helsinki 1964 as revised in 2013 and the International Conference of Harmonization Guidelines for Good Clinical Practice. This study was approved by the Institutional Review Board of Seoul National University Hospital (approval number: 1707–087-870, protocol version 2.1) and was registered at http://www.clinicaltrials.gov (NCT03273751). We will conduct this study at Seoul National University Hospital. A Data Monitoring Committee was established by the personnel who are independent of study organizers. This committee will monitor participant enrollment, data management, the accuracy of information on the case report form, and compliance to the trial protocol every 6 months.

### Randomization and blinding

After the initial enrollment, participants will be randomly assigned in a 1:1 ratio to either the RIPC or the control group according to Internet-based computer-generated random numbers in block sizes of 4 or 6 (http://www.sealedenvelope.com). Group allocations will be concealed from the investigators using opaque envelopes. The random assignment will be conducted by a third party independent of the study, and the assignment records will not be disclosed until the end of the study. On the day of the surgery, the opaque envelope containing the group allocation will be delivered to an anesthesiologist who is not involved in the study and is responsible for patient care and the RIPC intervention. Participants, urologic surgeons, post-anesthesia care staff, data collectors, and investigators assessing outcome data will be blinded to the treatment allocation to minimize potential sources of bias.

### Surgical and anesthetic procedures

The surgical procedure and anesthesia will be performed according to the standard of our hospital. Anesthesia will be induced with 1.5–2 mg/kg of an intravenous bolus of propofol and continuous remifentanil infusion (effect site concentration of 2–5 ng/ml) using a target-controlled infusion pump (Orchestra®; Fresenius Kabi, Bad Homburg, Germany). After loss of consciousness, rocuronium 0.6 mg/kg will be administered intravenously to facilitate endotracheal intubation. Anesthesia will be maintained with desflurane or sevoflurane using a concentration of 1–1.5 minimum alveolar concentration.

After the patients are put in a right or left upper lateral position for the surgery, a disposable NIRS sensor (INVOS™ Cerebral/Somatic Oximetry Adult Sensor, Medtronic, MN, USA) will be applied directly to the flank area that overlies the opposite kidney that is not undergoing surgery to monitor renal regional oxygen saturation (rSO_2_) under ultrasound guidance [25]. Renal rSO_2_ will be continuously monitored with NIRS (INVOS™ 5100C Cerebral/Somatic Oximeter, Medtronic, MN, USA) until the end of the surgery and rSO_2_ values will be recorded at intervals of 10 min.

### Interventions

After the induction of anesthesia and before renal artery cross-clamping, patients assigned to the RIPC group will receive the RIPC protocol using the upper arm. The RIPC protocol will be performed using an automated cuff-inflator, which consisted of four cycles of 5-min inflations at a blood pressure cuff to 250 mmHg (or at least to a pressure 50 mmHg higher than the systolic arterial pressure), followed by 5-min deflation of a blood pressure cuff. In patients assigned to the control group, a blood pressure cuff will also placed on the upper arm but without cuff inflation during the study period. The intervention will be performed by an anesthesiologist who is independent of this study.

### Study endpoints

The primary outcome is serum creatinine level 1 day after partial nephrectomy, as an index of postoperative kidney function. The secondary outcomes include the incidence of postoperative AKI and urinary biomarkers including urinary creatinine, microalbumin, β-2 microglobulin, and NAG measured immediately, and 1 day and 2 weeks after the partial nephrectomy (Fig. 2) [17–22]. The diagnosis of postoperative AKI will be based on the serum creatinine criteria of the Kidney Disease Improving Global Outcomes (KDIGO) criteria [26]. Estimated GFR (eGFR) measured immediately, and at 1 and 3 days, and 2 weeks after partial nephrectomy and renal rSO_2_ of the opposite kidney measured at 10-min intervals from the induction of anesthesia to the end of surgery will also be investigated as secondary outcomes. eGFRs will be calculated with the abbreviated isotope dilution mass spectrometry-Modification in Diet and Renal Disease Study equation, which is $$ \mathrm{eGFR}\ \left(\mathrm{ml}/\min /1.73\ {\mathrm{m}}^2\right)=175\times {\left(\mathrm{serum}\ \mathrm{creatinine}\right)}^{-1.154}\times {\left(\mathrm{age}\right)}^{-0.203}\times 0.742\ \left(\mathrm{if}\ \mathrm{female}\right)\times 1.212\ \left(\mathrm{if}\ \mathrm{black}\right) $$ [27].

**Fig. 2 Fig2:**
[figure not shown]
Flow diagram of measurements in the study. *sCr* serum creatinine, *eGFR* estimated glomerular filtration rate, *Hb* hemoglobin, *RIPC* remote ischemic preconditioning, *I*  ischemia, *R*  reperfusion, *rSO*_*2*_ regional oxygen saturation, *PACU* post-anesthesia care unit. Urinary biomarkers, including urinary creatinine, microalbumin, β-2 microglobulin, and *N*-acetyl-beta-D-glucosaminidase will be measured

Also, GFR measured by ^99m^Tc-DTPA renal scintigraphy will be obtained for a preoperative baseline and at 6 and 12 months after surgery.

### Data collection

Preoperative characteristics including age, sex, Body Mass Index, baseline values of serum creatinine concentration, eGFR, hemoglobin, ^99m^Tc-DTPA renal scintigraphy data, underlying diseases, medication status, smoking, and alcohol consumption will be collected.

We will collect surgery and anesthesia-related data including the R.E.N.A.L. nephrometry score [28], which are summarized in Table 1. Postoperative data will be assessed including the length of hospital stay, length of intensive care unit (ICU) stay, incidences of postoperative complications such as reoperation, postoperative wound infection, venous thromboembolism, myocardial infarction, and cerebrovascular accident.

**Table 1 Tab1:** Intraoperative data collection

Category	Variables
Surgery-related	Duration of surgery
	Type of partial nephrectomy (open/ laparoscopic/ robotic)
	Cold/warm ischemic
	Duration of renal ischemia
	Estimated blood loss
	R.E.N.A.L. nephrometry score
Anesthesia-related	Mean arterial pressure (lowest and highest)
	Total dose of anesthetics (propofol and remifentanil)
	Mean dose of anesthetics (sevoflurane or desflurane)
	Dose of vasopressors (ephedrine, phenylephrine, and calcium chloride)
	Dose of mannitol infused during surgery
	Urine output
	Total crystalloid/ colloid infused
	Blood transfusion amount
	Intraoperative complications

In our trial, all data will be entered electronically. Participant files are to be stored in numerical order and stored in an accessible and secure manner and place. Participant files will be maintained in storage for 3 years after completion of the study. Electronic data errors will be detected by programs designed to detect missing data or specific errors in the data.

### Safety endpoints

Safety outcomes regarding RIPC will be collected as follows. We will inspect and ask patients about ecchymosis or any skin change and symptoms including paresthesia, pain, or numbness where the RIPC was applied. We will monitor patients with a conventional three-lead electrocardiogram, pulse oximetry, and non-invasive arterial blood pressure measurements. Invasive radial arterial pressure monitoring and arterial blood gas analysis will be performed during surgery.

### Sample size

To determine the sample size, we reviewed serum creatinine changes in 20 patients who underwent partial nephrectomy. The mean value of serum creatinine was 1.60 mg/dl, and the standard deviation was 0.54 mg/dl at 1 day after partial nephrectomy. Assuming that the serum creatinine levels in the RIPC group were significantly lower than the levels in the control group by more than 0.35 mg/dl at 1 day after partial nephrectomy, 39 patients per group were required with a two-sided alpha-error of 0.05 and 80% power. Considering the 10% dropout rate, eight patients were added. The final sample size was determined to be 43 patients per group.

### Statistical analysis

Data will be expressed as mean (standard deviation), median (interquartile range) or the number of patients (%). The normality of distribution of data will be tested by the Kolmogorov-Smirnov test. To compare the outcome variables and baseline characteristics between the RIPC and the control group, Student’s *t* test or the Mann Whitney *U* test will be used for continuous variables depending on the distribution of data and the chi-square test or Fisher’s exact test will be used for categorical variables depending on the expected counts. For the comparison of the time-dependent measurement of serum creatinine, eGFR, urinary biomarkers, and renal rSO_2_ of the opposite kidney, repeated measures analysis of variance will be used to assess the changes within and between groups over time. The presence and incidence of missing data will be reported. Multiple imputations using the Markov chain Monte Carlo algorithm will be performed for handling missing values in our study data. Multivariable logistic regression analysis will be performed to adjust for potential confounding factors known to affect the risk of AKI including surgical parameters shown in Table 1 and patient characteristics (age, sex, history of hypertension, diabetes mellitus, renal insufficiency, and congestive heart failure). We planned to perform subgroup analysis based on surgical modalities and R.E.N.A.L. nephrometry score.

Data will be analyzed using SPSS software (SPSS version 24.0, Chicago IL, USA). G*power (version 3.1.9.2, Universität Düsseldorf, Düsseldorf, Germany) was used to calculate the sample size. A *P* < 0.05 will be considered statistically significant. Bonferroni correction for multiple measurements will be used to reduce type 1 error.

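### A normality test on the trial data chooses the primary test, and one of its two branches does not estimate the 0.35 mg/dl mean difference the trial is sized on

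*Protocol article*

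**What the plan says.** The Study endpoints section fixes the outcome: "The primary outcome is serum creatinine level 1 day after partial nephrectomy".

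The Statistical analysis section sets the rule for comparing the arms. First, "The normality of distribution of data will be tested by the Kolmogorov-Smirnov test". Then, under a purpose clause that reads "To compare the outcome variables and baseline characteristics between the RIPC and the control group", it names Student's t and Mann-Whitney U and says that the "test will be used for continuous variables depending on the distribution of data". The primary outcome is a continuous outcome variable, it is not exempted, and no other two-group comparison at day 1 is given.

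Two further statements in that section bear on creatinine. For measurements over time, "repeated measures analysis of variance will be used to assess the changes within and between groups over time". For incomplete data, "Multiple imputations using the Markov chain Monte Carlo algorithm will be performed for handling missing values in our study data".

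The Sample size section works on the scale of means. From 20 reviewed patients, "The mean value of serum creatinine was 1.60 mg/dl, and the standard deviation was 0.54 mg/dl at 1 day after partial nephrectomy", and creatinine in the RIPC arm is assumed to be "lower than the levels in the control group by more than 0.35 mg/dl at 1 day after partial nephrectomy". The Discussion reads that same 0.35 mg/dl against the 0.3 mg/dl rise that defines stage 1 AKI.

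**The concern.** The article does not merely leave the primary test unnamed. It states a rule under which the trial's own data name it. The two branches answer different questions. Student's t goes with a difference in mean creatinine in mg/dl, the quantity used to size the trial and to judge clinical relevance. Mann-Whitney goes with the probability that a patient in one arm has a lower value than a patient in the other. If the rank branch is taken, the 0.35 mg/dl hypothesis gets no direct answer.

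The selector is also weak at this sample size, and its outcome turns on details that the rule leaves open: corrected or uncorrected critical values, and pooled data or each arm separately. Two analysts who both follow the text could therefore report different primary tests on the same data.

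**Working it through.** **Inputs.** From Sample size: control mean 1.60 mg/dl, SD 0.54 mg/dl, difference 0.35 mg/dl, two-sided alpha 0.05, power 80%, 39 per group, 43 after dropout. From Randomization and blinding: 1:1 allocation. The shape of the creatinine distribution and the correlation of day-1 with preoperative creatinine are not given, so both are assumed and varied.

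**1. The plan's own figure.** Standardised difference: 0.35 / 0.54 = 0.648. Noncentrality of the two-sample t-test at n per arm: 0.648 × √(n/2). The exact power is 79.6% at n = 38 and 80.7% at n = 39, so 39 per group is reproduced as a t-test on means. Then 39 × 1.10 = 42.9, or 43, where power is 84.4%. The design calculation thus belongs to the t branch only.

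**2. How often each branch is taken.** There were 20,000 simulated trials per scenario, with 39 per arm, means 1.60 and 1.25, and SD 0.54 in both arms. The log-normal control arm has σ = √ln(1 + (0.54/1.60)²) = 0.328 and skewness of about 1.05. At the 5% level the critical distance for 39 values is 0.213 uncorrected and 0.140 with Lilliefors. For 78 pooled values it is 0.151 and 0.100.

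| Assumed shape | Mann-Whitney chosen, Lilliefors (pooled / per arm) | Mann-Whitney chosen, uncorrected (pooled / per arm) | t and Mann-Whitney disagree at 0.05 |
|---|---|---|---|
| Normal | 5.0% / 10.0% | 0% / 0% | 5.1% |
| Gamma | 28.4% / 37.8% | 0.7% / 0.7% | 6.5% |
| Log-normal | 52.7% / 62.9% | 4.2% / 3.9% | 9.9% |

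Taking the null and the planned effect together, the log-normal ranges are 53–63% with Lilliefors and 2–5% uncorrected. In a single log-normal arm of 39, the Lilliefors test detects the non-normality 32% of the time, against 53% for Shapiro-Wilk.

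**3. Error rates of the two-stage rule.** In the same simulation, type I error was 4.7% to 5.5% over all shapes and ways of running the test. At the planned effect, fixed t had about 81% power. The two-stage rule had about 80% for normal data, 81–83% for gamma and 81–88% for log-normal.

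**4. How often the rule changes the verdict.** The verdict can differ from a fixed t-test only where Mann-Whitney is chosen and the two tests also disagree. The last column of the table is therefore an upper bound, not the answer. A second log-normal simulation (39 per arm, 3,000 trials) multiplied RIPC values by a ratio, so the RIPC SD shrinks too: at 1.25/1.60 = 0.781 it is 0.54 × 0.781 = 0.42.

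| Ratio | Power, fixed t | Power, two-stage (Lilliefors / uncorrected) | Verdict changed (Lilliefors / uncorrected) |
|---|---|---|---|
| 0.781 (planned) | 89.9% | 89.9% / 89.8% | 3.4% / 0.5% |
| 0.85 | 54.1% | 54.6% / 54.3% | 6.0% / 0.6% |

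**5. Power of a fixed, baseline-adjusted analysis in mg/dl.** The residual SD is 0.54 × √(1 − ρ²), and the noncentrality is (0.35 / residual SD) × √(39/2), with 75 degrees of freedom after adjustment.

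| Assumed ρ | Residual SD | Noncentrality | Power at 39 per arm |
|---|---|---|---|
| Unadjusted | 0.540 | 2.86 | 81% |
| 0.3 | 0.515 | 3.00 | 84% |
| 0.5 | 0.468 | 3.30 | 90% |
| 0.7 | 0.386 | 4.01 | 98% |

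**The case against.** The strongest reply is that the rule does little numerical damage. That is right. A reader might infer that pre-testing inflates the type I error or wastes power, and the simulations show neither. The 5–10% disagreement between the two tests also overstates the effect on the result, because the rule departs from a fixed t-test less often than that.

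A reader might also infer that the rank branch cannot be combined with the planned multiple imputation. It can. Pooling P(X<Y) and its standard error by Rubin's rules over 10 imputations, with 10% missing, gave a type I error of 5.7% (2,000 trials, Monte Carlo standard error about 0.5 points). At most, a bare Mann-Whitney P value does not pool directly. The pooling method is something an article may leave to a fuller document.

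Nor do the documents show that creatinine is skewed here. They give only a mean and SD from 20 patients. With gamma instead of log-normal data, the Lilliefors branch rate falls to 28–38%.

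The power gain in step 5 comes from baseline adjustment, not from removing the pre-test. It depends on a correlation the article does not give, and the restriction of preoperative creatinine to 1.4 mg/dl or less in Setting and participants leaves that value uncertain.

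Finally, an unseen analysis plan might name one test. It would then have to override a rule that the article states outright. The repeated measures analysis does not settle the matter either: it concerns change over time and is not named as the primary comparison. What survives all this is the pre-specification point.

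**Conclusion.** The point holds as one of pre-specification and interpretability. The primary test is chosen from the trial data, and one of the two possible outcomes of that choice does not estimate the quantity the trial was sized on. Under assumed log-normal data, the chance of landing on that branch runs from about 2% to 63% according to how the test is run. The consequence for the significance verdict is modest: roughly 0.5–6% of trials in the multiplicative log-normal model. With log-normal data and a common SD of 0.54, it cannot exceed the 10% disagreement rate. Type I error near 5% and undiminished power hold for all three shapes examined.

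That the rule covers day-1 creatinine is read from its general reference to outcome variables, with no exemption stated. The change is worth making before unblinding, but the defect does not threaten the validity of the trial.

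**What to change.** Remove the normality test as the selector for the primary outcome and name one primary analysis: ANCOVA of day-1 serum creatinine on arm and preoperative serum creatinine. Report it as an adjusted mean difference in mg/dl with a 95% CI, pooled over the imputations by Rubin's rules. Keep Mann-Whitney and a log-scale analysis as labelled sensitivity analyses. A log-scale ratio should not be the primary result, because it too would leave the 0.35 mg/dl hypothesis without a direct answer.

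The cost is a change of wording before unblinding. Preoperative creatinine is already collected (Data collection), and the Trial status section reports 46 of 86 patients enrolled by June 2018. No more patients are needed. Even an unadjusted t-test fixed in advance would cure the defect at the planned n. The price is reliance on a comparison of means if the data prove skewed, which the sensitivity analyses would show.

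### The primary day-1 creatinine test leaves out the preoperative creatinine the trial already collects, which costs precision but not validity

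*Protocol article*

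**What the plan says.** Study endpoints defines the outcome as a level, not a change: "The primary outcome is serum creatinine level 1 day after partial nephrectomy, as an index of postoperative kidney function".

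Statistical analysis then sets the test. It opens with "To compare the outcome variables and baseline characteristics between the RIPC and the control group" and continues with Student's t "test or the Mann Whitney *U* test will be used for continuous variables depending on the distribution of data". No covariate is attached to this comparison. Sample size is built on the same unadjusted contrast: "The mean value of serum creatinine was 1.60 mg/dl, and the standard deviation was 0.54 mg/dl at 1 day after partial nephrectomy", with a target difference of 0.35 mg/dl and 39 patients per group.

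Data collection lists "baseline values of serum creatinine concentration, eGFR, hemoglobin" among the preoperative variables, so the natural covariate is in the database.

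Two other planned analyses come close to the issue:

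- "Multivariable logistic regression analysis will be performed to adjust for potential confounding factors known to affect the risk of AKI". This concerns a binary secondary outcome. The patient characteristics it names include renal insufficiency but not baseline creatinine.
- For serum creatinine and other series, "repeated measures analysis of variance will be used to assess the changes within and between groups over time". The text does not say whether the preoperative value is one of the time points, and it does not make this the primary test.

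**The concern.** A patient's creatinine on day 1 reflects both where the patient started and what the operation did. The article's own reasoning concerns the second part. Its hypothesis in Background is about a smaller rise in creatinine, and its Discussion sets the 0.35 mg/dl target beside the KDIGO increase of 0.3 mg/dl. A comparison of raw levels leaves variation in starting values in the error term of the one comparison the trial is powered for.

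Two things are at stake. The confidence interval for the RIPC effect is wider than the collected data allow. And if the arms happen to differ in preoperative creatinine, the primary estimate carries part of that difference. Randomization and blinding describes blocks of 4 or 6 and mentions no stratification by baseline renal function. The plan compares baseline characteristics between arms but does not say how the primary result would account for a difference.

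**Working it through.** **Inputs.** From Sample size: difference 0.35 mg/dl, SD 0.54 mg/dl, two-sided alpha 0.05, 39 per group. Not in the article, so assumed: the correlation ρ between preoperative and day-1 creatinine (0.2 to 0.7) and, in step 3 only, a preoperative SD of 0.20 mg/dl.

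**Step 1: the plan's own figure.** The standardised difference is 0.35/0.54 = 0.648. The standard error is 0.54 × √(2/39) = 0.122 mg/dl. A noncentral t calculation with 2 × 39 − 2 = 76 degrees of freedom gives 80.7% power at 39 per group and 79.6% at 38. So 39 is the smallest adequate size, as stated, and 39 × 1.1 = 42.9 gives the stated 43.

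**Step 2: the same trial with baseline adjustment.** ANCOVA reduces the residual SD to 0.54 × √(1 − ρ²) and uses one more degree of freedom (75). At 39 per group:

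| ρ (assumed) | Residual SD | SE of difference | Power for 0.35 | Difference detectable with 80% power |
|---|---|---|---|---|
| unadjusted | 0.540 | 0.122 | 80.7% | 0.347 |
| 0.2 | 0.529 | 0.120 | 82.2% | 0.340 |
| 0.3 | 0.515 | 0.117 | 84.2% | 0.331 |
| 0.4 | 0.495 | 0.112 | 86.9% | 0.318 |
| 0.5 | 0.468 | 0.106 | 90.4% | 0.301 |
| 0.7 | 0.386 | 0.087 | 97.7% | 0.248 |

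**Step 3: which part of the range is plausible.** The regression slope of day-1 on baseline creatinine is ρ × 0.54 / (baseline SD). Setting and participants excludes preoperative creatinine above 1.4 mg/dl, which narrows the baseline spread. If the baseline SD were 0.20, ρ = 0.4, 0.5 and 0.7 would need slopes of 1.08, 1.35 and 1.89, meaning that the rise after surgery grows with the starting value. If the rise is unrelated to the starting value (slope 1), ρ = 0.20/0.54 = 0.37 and power is about 86%.

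**Step 4: chance imbalance.** Suppose the arms differ at baseline by 1.96 standard errors; a difference at least that large, in either direction, has a 5% chance. The unadjusted day-1 difference then moves by ρ × 1.96 × 0.122 mg/dl, whatever the baseline SD. That is 0.07, 0.12 and 0.17 mg/dl at ρ = 0.3, 0.5 and 0.7, against a target of 0.35.

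Given that imbalance and no treatment effect, the test statistic is approximately normal with mean 1.96ρ and variance 1 − ρ². The chance of a significant result is then about 8%, 13% and 20%. At an imbalance of one standard error it is 5.0%, 4.8% and 3.9%. Over all randomisations the rate averages 5%.

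**The case against.** The strongest reply is that nothing here is an error. In a 1:1 randomised trial the two-sample comparison is unbiased over randomisation and has 5% type I error. Endpoint, sample size and test agree with one another, and the trial reaches its 80% target without adjustment. All of this stands. It makes the point one of efficiency, not of correctness. It does not remove the point, because the test is a stated choice rather than a detail left open.

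A second reply is that baseline is not ignored across the trial. AKI by the KDIGO creatinine criteria needs a reference value, and the repeated measures analysis may include the preoperative measurement. This also stands, but neither analysis is the primary test.

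A third reply is that the gain may be small. At ρ = 0.2 it is only 1.5 percentage points of power (82.2% against 80.7%), and the 1.4 mg/dl exclusion could keep ρ low. That is a fair limit on the size of the gain. Power still rises at every correlation tabulated.

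A fourth reply is that the plan keeps a Mann-Whitney branch for skewed data, which a raw-scale ANCOVA would not cover. That is correct, and the change has to provide for it.

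**Conclusion.** The point holds as a matter of precision. The primary comparison omits a covariate that is already collected. Adjusting for it would raise power at 39 per group from 80.7% to between about 82% and 98% for assumed correlations of 0.2 to 0.7. The upper end should not be taken as the expected gain: a slope of 1 with an assumed baseline SD of 0.20 mg/dl gives about 86%. These figures assume a linear relation and roughly normal residuals, and ρ is not in the article. The absence of adjustment is certain; the size of the gain is not.

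A reader might infer three stronger things that the article does not support:

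- **That the unadjusted test is biased or the sample size wrong.** Its error rate is 5% over randomisation, and the stated 39 reproduces.
- **That chance imbalance is a further harm on top of the lost power.** It is already part of the 0.122 mg/dl standard error. The higher error rates in step 4 apply only once a large imbalance has occurred.
- **That preoperative creatinine is used nowhere.** It may enter through the AKI definition and possibly the repeated measures analysis. It is absent only from the primary comparison.

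**What to change.** Before unblinding, state that the primary analysis is an ANCOVA of day-1 serum creatinine on treatment arm with preoperative serum creatinine as covariate, reported as an adjusted difference with its 95% CI. State also that both creatinine values will be log-transformed if the residuals are skewed, in place of the switch to the Mann-Whitney test; the effect is then a ratio of geometric means. Keep the unadjusted comparison as a sensitivity analysis.

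The cost is a short amendment to the analysis text. It needs no new measurements, no more patients and no change to the endpoint or sample size. Trial status reports 46 of 86 patients enrolled by June 2018, and the assignment records stay closed until the end of the study, so on the article's account the change could still be made blind.
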